#### Sample Size and Power

A power analysis using a bivariate latent growth curve model indicates a power of *β*=.82 for 160 participants to detect a moderate path coefficient (b=0.2) of cortisol reactivity on changes in psychopathology.

#### Experimental Design

This task uses a cross-sectional assessment of endocrine stress responses within the longitudinal study.

#### Measures

Endocrine stress responses provide a more proximate measure of stress compared to childhood adversity. We will assess stress responses through hair cortisol levels [103] and salivary cortisol measurements following a developmentally appropriate social stress test [94]. Hair cortisol levels will quantify the retrospective stress levels, while salivary cortisol will quantify the acute stress response.

For hair cortisol, we will collect 3 centimeters in length of scalp-nearest hair; this will contain cortisol information over the preceding 3 months. Salivary cortisol will be collected via fiber chewing before and after a social stress test (after 30-40 minutes). In the social stress test, the children are instructed to match stickers to animals to win a prize. Time pressure will be applied by a commenting experimenter and a toy traffic light that turns red and emits a buzzer sound [94,104]. Contractors will process salivary (Daacro) and hair (Dresden Lab service) samples.

#### Statistical Analysis Plan

The cortisol measures will be applied in a mediation model to examine LC-NE functioning in the association of stress response and psychopathology. We will further quantify the effect of LC-NE functioning in the association of childhood adversity and stress response.

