### Sample Size and Power

Sample sizes (n) were determined based on recruitment feasibility and the ability to detect moderate effects with a power of *β*>.80. For each task, we estimated the power by Monte Carlo simulations (k=1000) within respective models [97,98]. In the following sections, the sample size and power are reported, respectively, for each specific objective or task.

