##### Behavioral Measures

At each timepoint assessment of the behavioral measures, as described in Task 2.2, will include caregiver questionnaires (CBCL 4‐18) and the multiple-source assessment of childhood adversity (see Table 1).

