### Task 3.2: LC-NE Functioning Mediates the Effect of Stress Responses on the Development of Transdiagnostic Psychopathology

#### Participants

Participants in this study will comprise a subsample of 5‐6-year-olds (n=160) at one randomly selected timepoint (T2 or T3) from the large longitudinal cohort (Task 3.1).

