#### Expected Outcome

We expect a positive association between cortisol measures and psychopathology. Based on our model (Figure 1), we assume BPS and SEPR to mediate this direct effect. Higher BPS and SEPR are expected to explain an increased effect of hair cortisol levels and salivary cortisol response on the internalizing symptoms and the p-factor. Lower BPS is expected to be a protective factor on the negative impact of stress on psychopathology, which could represent a mechanism of resilience. Based on our preliminary work (see above), we expect an attenuated downregulation of salivary cortisol in response to the social stress test (ie, inefficient acute stress regulation) to be associated with higher internalizing symptoms and a higher p-factor. We expect this effect to be mediated by BPS as an index of LC-NE tonic activity.

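### Task 3.2 is titled and powered for change in psychopathology, but its stated analysis is a mediation model of an association with no change or earlier-CBCL term

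*Protocol article*

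**What the plan says.** All places are in the protocol article.

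- **Task 3.2, title:** "LC-NE Functioning Mediates the Effect of Stress Responses on the Development of Transdiagnostic Psychopathology".
- **Task 3.2, Sample Size and Power:** "A power analysis using a bivariate latent growth curve model" gives .82 (printed as β) for 160 children "to detect a moderate path coefficient (b=0.2) of cortisol reactivity on changes in psychopathology".
- **Task 3.2, Experimental Design:** the endocrine stress assessment is described as cross-sectional within the longitudinal study.
- **Task 3.2, Statistical Analysis Plan:** "The cortisol measures will be applied in a mediation model to examine LC-NE functioning in the association of stress response and psychopathology". One further sentence adds the role of LC-NE functioning between childhood adversity and stress response. No covariates and no timing of the outcome are given.
- **Task 3.2, Expected Outcome:** "We expect a positive association between cortisol measures and psychopathology", with BPS and SEPR as mediators.
- **Task 3.2, Participants:** the subsample is assessed at T2 or T3, never at T1.
- **Task 3.1, Behavioral Measures:** each time point "will include caregiver questionnaires (CBCL 4‐18) and the multiple-source assessment of childhood adversity". A T1 CBCL is therefore scheduled for every child who later takes the stress test.

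Control for earlier psychopathology is stated in Task 3.1, through autoregressive paths and as an exploratory covariate, and as a comparator in Work Package 4. No section carries it into Task 3.2.

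**The concern.** The title and the power calculation ask whether stress responses change the course of symptoms. The named analysis asks whether cortisol, LC-NE functioning and psychopathology are associated. A child with high symptoms at T1 may have both higher cortisol and higher CBCL scores a year or two later. A mediation model without the earlier score would show that as a path from stress response to psychopathology even if nothing had changed because of stress. The recruitment makes this plausible: the main source is an outpatient clinic, internalizing symptoms are deliberately over-recruited, and children from the general population are added, so wide differences in symptoms at entry are part of the design.

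The power statement is also for a different quantity. It concerns a direct path on change, whereas the analysis section concerns mediation and names no change outcome.

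**Working it through.** **1. The two sections side by side**

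| | Sample Size and Power | Statistical Analysis Plan |
|---|---|---|
| Model | bivariate latent growth curve | mediation model |
| Outcome | changes in psychopathology | psychopathology |
| Effect | direct path from cortisol reactivity | role of LC-NE functioning in the association |
| Earlier CBCL | implied by a growth model | not mentioned |

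As worded, these are not the same analysis, and no text links them.

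**2. The plan's own figure**

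The .82 comes from a simulation of a growth model. Alpha, slope variance, residual variance and wave correlations are not given, so it cannot be rebuilt. A simple proxy (standardized path b = 0.2, n = 160, 5% level) gives:

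- Two-sided, Fisher z: atanh(0.2)·√157 − 1.96 = 2.540 − 1.96 = 0.580, power 0.72.
- Two-sided, Wald: 0.2·√160/√(1 − 0.04) − 1.96 = 2.582 − 1.96 = 0.622, power 0.73.
- One-sided versions: 0.81 to 0.83.

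These proxies are not the growth model, so they neither confirm nor refute .82.

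**3. Power with and without T1 CBCL, if cortisol is unrelated to it**

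Inputs: b = 0.2 and n = 160 from the protocol; two-sided 5% and the T1-to-later CBCL correlation ρ are assumptions (0.5, range 0.3 to 0.7). T1 CBCL removes ρ² of the outcome variance:

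power = Φ( 0.2·√160 / √(0.96 − ρ²) − 1.96 )

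| ρ | 0.96 − ρ² | power |
|---|---|---|
| none (no T1 CBCL) | 0.96 | 0.73 |
| 0.3 | 0.87 | 0.77 |
| 0.5 | 0.71 | 0.85 |
| 0.7 | 0.47 | 0.96 |

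Using √157 in place of √160 changes these by less than 0.01.

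**4. False positives, if cortisol is related to T1 CBCL**

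Assume no effect on change, stability 0.5, and a correlation c between T1 CBCL and later cortisol. The unadjusted correlation is then r = 0.5c. With λ = r·√160/√(1 − r²), the rejection rate is Φ(λ − 1.96) + Φ(−λ − 1.96).

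| c | r | rejection, formula | rejection, simulation (4,000 samples) |
|---|---|---|---|
| 0.1 | 0.05 | 9.7% | 9.9% |
| 0.2 | 0.10 | 24.6% | 24.3% |
| 0.3 | 0.15 | 48.4% | 47.4% |

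At stability 0.7 the simulation gave 13%, 42% and 77%. With T1 CBCL in the model, rejection stayed between 4% and 6% throughout. With c = 0, both models held about 5%.

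**5. The two effects do not add up**

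Step 3 needs c = 0 and step 4 needs c > 0. If b = 0.2 is real, ρ = 0.5 and c = 0.2, the unadjusted correlation is 0.2 + 0.5·0.2 = 0.3. The unadjusted test then rejects in about 97% of samples and the adjusted one in about 84%. The unadjusted model does not lack power in that case; its extra rejections come from the carried-over symptoms.

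**The case against.** The analysis text is two sentences in a condensed article. It lists no covariates and never says that the outcome is a level. A reader might infer that the plan leaves T1 CBCL out on purpose. The document does not say so; it is silent. The general Sample Size and Power section also states: "For each task, we estimated the power by Monte Carlo simulations (k=1000) within respective models". Read with the Task 3.2 power paragraph, this suggests that a growth model of change may be intended, and mediation can be placed inside such a model. If so, most of the power loss and bias shown above would not arise. This stands, and it means the calculations describe the analysis as worded, not necessarily as intended. It does not remove the mismatch, because the section that defines the analysis never names the growth model.

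A reader might also infer that .82 is an unadjusted figure that T1 CBCL would raise. The power paragraph contradicts that: the figure is already for change.

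A further objection concerns the estimand. If stress reactivity or LC-NE functioning had already shaped symptoms by T1, adjusting for T1 CBCL removes part of the effect of interest. That is a fair reason to report the unadjusted association as well. Against it, hair cortisol covers only the preceding three months and salivary cortisol is acute, so T1 symptoms come before both measurement windows, and the title claims development. The objection is stronger for the mediator. The Preliminary Work reports BPS correlations of 0.69 to 0.81 between measurements over 12 months in 26 children, so adjusting for T1 BPS would remove about 48% to 66% of its variance (0.69² to 0.81²) and leave change in a stable trait.

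**Conclusion.** The point holds as an inconsistency with consequences. Task 3.2 is titled and powered for change. Its stated analysis and expected outcome are a mediation model of an association with no change or earlier-CBCL term. The stated power therefore does not describe the stated analysis, and the model as written cannot separate pre-existing symptoms from an effect on development.

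The sizes are illustrations. They rest on an assumed CBCL stability, an assumed correlation of cortisol with T1 CBCL, a two-sided 5% test, and a direct path rather than the mediated effect:

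- cortisol unrelated to T1 CBCL: power about 0.72-0.73 unadjusted, against 0.77 to 0.96 adjusted (stability 0.3 to 0.7);
- cortisol correlated 0.1 to 0.3 with T1 CBCL, stability 0.5: about 10% to 48% false-positive paths unadjusted.

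These are alternative scenarios. The documents do not support saying that the analysis suffers both at once, that it excludes T1 CBCL, or that .82 is wrong.

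**What to change.** Make the Sample Size and Power and Statistical Analysis Plan sections of Task 3.2 describe one model of change, in either of two ways:

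1. keep the mediation model and enter the T1 CBCL score of the same factor (internalizing, externalizing or total) on the outcome, as a covariate or autoregressive path; or
2. place the mediation inside the bivariate latent growth curve model that was powered.

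Then restate the power for that model, preferably for the mediated effect as well as the direct path. Report the unadjusted association alongside. Adjustment of the mediator for T1 BPS or SEPR should be at most a sensitivity analysis.

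The cost is revised wording and one new simulation. No visit or measure is added, since T1 CBCL is scheduled for the whole cohort. The longitudinal study is planned to start in April 2026, so the choice can be fixed before its outcome data exist. The downside is one more covariate per model at n=160 under the first option, and an estimate that refers to change rather than to the total association.

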#### Expected Outcome

We expect a positive association between cortisol measures and psychopathology. Based on our model (Figure 1), we assume BPS and SEPR to mediate this direct effect. Higher BPS and SEPR are expected to explain an increased effect of hair cortisol levels and salivary cortisol response on the internalizing symptoms and the p-factor. Lower BPS is expected to be a protective factor on the negative impact of stress on psychopathology, which could represent a mechanism of resilience. Based on our preliminary work (see above), we expect an attenuated downregulation of salivary cortisol in response to the social stress test (ie, inefficient acute stress regulation) to be associated with higher internalizing symptoms and a higher p-factor. We expect this effect to be mediated by BPS as an index of LC-NE tonic activity.

#### Risk Assessment

Childhood adversity might not be disclosed by caregivers if they are also the perpetrators, while child reports on adversity might be unreliable. To mitigate the underreporting biases, we will implement the multiple-sources approach to adversity. In addition, any reports on adversity will be evaluated according to our in-house reporting guidelines and may lead to further actions.

### Work Package 4 (Objective 4): Development of an Objective Tool of Risk Prediction in the Preschool Age Based on the Pupillometric Measures of LC-NE Functioning

#### Participants

The full sample was recruited during work packages 2 and 3.

#### Sample Size

The full sample consists of the 300 participants assessed in task 2.2.

#### Experimental Design

The findings of Objectives 2 and 3 will be used to enrich a probabilistic model in the full sample (n=300) that assigns individual risk based on LC-NE functioning in the preschool age. This will be evaluated as a tool of quantitative risk prediction for future psychopathology. We will operationalize risk probability within a normative model of transdiagnostic psychopathology [105]. A reference cohort will be defined from a subsample of participants that did not develop clinically relevant transdiagnostic psychopathology. This cohort will be applied to estimate a normative development model (ie, output) as a function of LC-NE tonic and phasic activity profiles. It defines a range of LC-NE functioning variation that is associated with a low risk. The model can then be applied to withheld data, that is, individuals who did develop transdiagnostic psychopathology. This allows one to quantify a numeric deviation of LC-NE functioning from normative ranges. The numeric deviation is then applied as a predictor of psychopathology in linear models that represent an individual risk prediction. The performance of individual risk prediction based on LC-NE functioning will be compared to the predictive validity of available covariates, confirmed by v-fold validation, and implemented in the outpatient clinic for external validation in independent data.

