#### Statistical Analysis Plan

Structural equation models will be applied to estimate the associations between the latent constructs (LC-NE functioning, transdiagnostic psychopathology, and childhood adversity). A best-fit path model will be used to reduce the complexity of the structural equation in the longitudinal study of Objective 3. A latent mediation model, in which LC-NE functioning is expected to mediate an association between previous childhood adversity and transdiagnostic psychopathology, will be applied. Independent models for BPS, SEPR, and each transdiagnostic factor will be estimated. Classification approaches will be applied in exploratory analyses to identify LC-NE function profiles in subgroups of psychopathology.

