### Work Package 3 (Objective 3): Prospective Effect of LC-NE Functioning in a Developmental Model of Vulnerability and Stress

#### Task 3.1: LC-NE Functioning Predicts Later Transdiagnostic Psychopathology.

##### Participants

The study will follow the sample of 300 preschool-aged children, initially assessed in Task 2.2 at 4‐6 years of age across 3 time points.

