The LOCUS-MENTAL study uses targeted strategies across its work packages to manage missing data and ensure robust longitudinal findings. Work package 1 focuses on feasibility measures by using passive and child-friendly paradigms to achieve a projected completion rate of over 80%. Statistical analysis will exclude children that have per-task data validity rates of less than 50% or more than one missing task. The auditory oddball task is a marker task that is required to be included in the statistical analysis. We established standardized procedures of pupillometry data preprocessing to address within-trial missing data due to inattention. Work package 2 addresses high-burden EEG assessments by designating them as “more optional” in the context of the overall project, which allows for an expected 30% attrition rate without hindering subsequent study objectives. For the longitudinal assessments in work package 3, the study implements retention strategies like online data collection and locator documents. In addition, the statistical framework of work package 3 includes LMM and structural equation modeling to handle intermittent missingness across time points. Questionnaire data on an item level with per-measure missing rates up to 20% will be addressed by Multiple Imputation by Chained Equations (MICE) that preserves statistical power under the missing at random assumptions. However, children with increased irritability or increased burden may be more likely to drop out (ie, missing not at random or MNAR). Thus, pattern mixture models will be applied as a sensitivity analysis to determine if the developmental trajectories of LC-NE functioning are biased by specific attrition patterns. In addition, Inverse Probability Weighting (IPW) in the longitudinal data analysis can be used to adjust for non-random attrition by weighting the remaining participants based on baseline characteristics (eg, socioeconomic status or initial psychopathology scores) that predict dropout. Missing bio samples will be addressed by case-wise exclusion in the specific subanalysis. Finally, work package 4 uses v-fold validation to evaluate the predictive stability of the risk prediction tool.

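### Choices carried from Objectives 2 and 3 into the work package 4 risk model make its v-fold result optimistic if they are made outside the folds

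*Protocol article*

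**What the plan says.** Work Package 4, Sample Size: "The full sample consists of the 300 participants assessed in task 2.2". Task 3.1, Participants, uses the same cohort: "The study will follow the sample of 300 preschool-aged children, initially assessed in Task 2.2". One group of children therefore supplies the cross-sectional findings (Task 2.2), the prospective findings (Task 3.1) and the risk model. Psychopathology is measured by the CBCL throughout.

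Two data-driven steps are stated in Task 2.2, Statistical Analysis Plan: "A best-fit path model will be used to reduce the complexity of the structural equation in the longitudinal study of Objective 3", and "Classification approaches will be applied in exploratory analyses to identify LC-NE function profiles in subgroups of psychopathology". Task 3.1, Expected Outcome, says that the core analysis will be informed by Task 2.2 and that its models will be explored for covariate effects.

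Work Package 4, Experimental Design, then says: "The findings of Objectives 2 and 3 will be used to enrich a probabilistic model in the full sample (n=300"). It ends by stating that performance will be compared with available covariates, confirmed by v-fold validation, and taken to the outpatient clinic for external validation. The missing-data paragraph under Ethical Considerations repeats that "work package 4 uses v-fold validation to evaluate the predictive stability of the risk prediction tool". Neither place says which steps are redone within a fold.

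**The concern.** Cross-validation gives an honest estimate only of the steps that are repeated without the held-out children. If a path structure, a profile or a set of indices was picked using all 300 children's CBCL scores, each held-out fold has already helped to pick it. Splitting the data afterwards tests the coefficients but not the choice. The leak is direct for Task 3.1, whose follow-up CBCL is what the tool predicts. It is indirect for Task 2.2, through the stability of CBCL scores over time.

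Work Package 4, Expected Outcome, claims added explained variance over previous psychopathology, adversity and cognitive ability. Such an increment may be small, and a small increment is what this kind of optimism can imitate. The tool is meant to inform support for individual children, so its internal performance should not be overstated.

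**Working it through.** The plan gives no AUC, R², fold count or number of candidate predictors for work package 4, so there is no figure of its own to reproduce. The check has two parts.

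**Order of steps in the text.** (a) Task 2.2 and Task 3.1 use all 300 children and their CBCL scores. (b) Their findings enrich the model in the full sample. (c) v-fold validation follows. Read in that order, any choice made at (a) precedes the split at (c). Work package 1 is not a source of the leak: its battery reduction rests on intercorrelations in the 90-child validation phase, and Table 1 does not list the CBCL for Objective 1.

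**Size under the null (no true association).**

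Inputs from the article:
- n = 300.
- Retention of 73.5% (Task 3.1, Risk Assessment) gives 0.735 × 300 ≈ 220.
- 4 battery tasks × 2 metrics (BPS, SEPR) = 8 candidate indices.

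Assumptions:
- The best 1 to 3 of the 8 indices are chosen by correlation with the outcome.
- 10 folds and a linear model.
- Correlation across tasks is .75 for BPS and .3 for SEPR, or zero in the independent-index variant.

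Measure: cross-validated R² = 1 − Σ(y − out-of-fold prediction)² / Σ(y − baseline)². The baseline can be the whole-sample mean (stricter) or the training-fold mean. This changes the levels but hardly the ratio.

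Share of null studies with cross-validated R² above zero, correlated indices, one fixed outcome:

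| Baseline | Chosen outside folds | Chosen inside folds | Prespecified BPS and SEPR composites |
|---|---|---|---|
| Whole-sample mean | 14%–28% | 5%–13% | 4%–7% |
| Training-fold mean | 32%–65% | 12%–24% | 13%–18% |

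Ratios of outside to inside are 14/5 = 2.8 and 28/13 = 2.2 in the first row, and 32/12 = 2.7 and 65/24 = 2.7 in the second. Mean R² with choice outside the folds stays close to zero: −0.004 to −0.017 in the first row and within about 0.006 of zero in the second.

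Sensitivity with independent indices (whole-sample baseline for R², binary outcome set at the top 30% for AUC):
- 2 of 8 chosen, n = 300: 38% outside against 7% inside (38/7 = 5.4); mean AUC 0.559 against 0.499.
- 2 of 8 chosen, n = 220: 35% against 7% (35/7 = 5.0); mean AUC 0.571 against 0.499.
- Wider search at n = 300: mean AUC outside the folds is 0.583 for 3 of 16 and 0.619 for 5 of 40.
- Two predictors fixed in advance: mean AUC 0.500 at n = 300 and 0.498 at n = 220, so no optimism.

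The factor of two to three therefore belongs to correlated indices. It is about five if the indices are independent.

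**The case against.** The best defence is that no selection of indices is stated. The text says enrich, and the input it names is tonic and phasic LC-NE activity, that is, BPS and SEPR. Both are defined under Neurophysiological Measures, and their expected directions are given in Task 2.2 and Task 3.1. Task 2.2 plans a separate model for each index and each CBCL factor. The content of the folds is detail that an analysis plan may settle, and external validation is promised in the same sentence as v-fold.

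Much of this stands. A reader might infer that v-fold cannot detect the selection at all, or that the tool will look useful even without any signal. The documents support neither. Nesting is not ruled out, mean null R² stays near zero, and most null studies show no gain in most of the settings examined. A larger contrast, 23%–46% of null studies above zero against 7%–12%, arises if the analyst also picks the best of three outcomes on all the data. The protocol makes no such choice, so that contrast should not be used.

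The defence does not remove the point. The best-fit model and outcome-related profiles are stated steps, they are stated to feed the model in the full sample, and confirmation is attached to the v-fold result. That is a stated order of work, not only an omitted detail. The external check has no stated size or timing.

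**Conclusion.** The point holds in a limited form. Outcome-informed choices from Objectives 2 and 3, if made outside the folds, make the internal v-fold estimate optimistic, and confirmed is then too strong a word for it. There is no optimism if only prespecified BPS and SEPR are used. There is a modest amount if a few of about 8 correlated indices are chosen, and more as the search widens.

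These sizes rest on an assumed number of indices, assumed correlations and a linear model on raw indices. They do not simulate the normative deviation score, or the increment over previous psychopathology, adversity and cognitive ability that the article expects to show. The criticism applies to the internal result and not to the whole validation plan, since the clinic data could expose the optimism.

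A separate question, not counted here, is that the norm is fitted to children selected by outcome ("A reference cohort will be defined from a subsample of participants that did not develop clinically relevant transdiagnostic psychopathology") while only those who developed psychopathology are called withheld.

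**What to change.** Add one of two statements to Work Package 4, Experimental Design:

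1. The predictors are fixed now as BPS and SEPR composites across tasks, formed without reference to the CBCL, with the directions already in Task 3.1, Expected Outcome: higher BPS for the p-factor, higher SEPR for internalizing, lower SEPR for externalizing.
2. Every choice based on Objective 2 or 3 (path structure, profiles, indices) is repeated using only the training children in each fold, and only that result is reported as validated.

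In either case, describe v-fold as an internal check, both there and in the missing-data paragraph, and reserve confirmed for the independent clinic data.

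The cost is a few sentences, some computing time under the second option, and possibly slightly lower reported performance. The longitudinal phase runs to March 2029, so this can be settled before follow-up outcomes are complete.

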### Main Objectives

The primary aim of LOCUS-MENTAL is to establish pupillometric measures of LC-NE functioning as a predictor of transdiagnostic psychopathology in childhood. We hypothesize that LC-NE functioning represents a fundamental neurobiological mechanism in the development of MHD that could serve as a biomarker for early risk detection. Transdiagnostic psychopathology is assessed with the caregiver-reported Child Behavior Checklist (CBCL), where clinical relevance is defined as reaching established cutoffs (T>60). LC-NE functioning is assessed with pupillometry. The study outcome could improve targeted prevention and intervention for MHD comorbidity in children. To achieve this aim, LOCUS-MENTAL is structured into 4 consecutive objectives, each with specific tasks within the following project plan (Figure 3).

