### Recruitment

The main recruitment avenues will be the outpatient clinic for early detection at the Department for Child and Adolescent Psychiatry at the Goethe University Hospital. In the help-seeking population, externalizing disorders might be overrepresented, which is why we will overrecruit preschoolers with internalizing symptoms. We aim for a representative sample by recruitment across all levels of psychopathology. This is why we will also recruit in the general population by distributing flyers with study information at local health care and public institutions, pediatricians, and day care facilities and promoting the study in targeted social media groups and channels. Exclusion criteria will be known genetic syndromes and neurological diseases. Caregivers will receive a summary report of their child’s assessment (eg, IQ evaluation) upon completion of each assessment wave.

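### Work Package 4 withholds only cases from the normative model and does not say that the norm is refitted within folds, so internal performance may be optimistic or specificity inestimable

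*Protocol article*

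**What the plan says.** The rule is in the protocol article, Work Package 4, Experimental Design. The training set is fixed first: "A reference cohort will be defined from a subsample of participants that did not develop clinically relevant transdiagnostic psychopathology". The norm follows: "This cohort will be applied to estimate a normative development model (ie, output) as a function of LC-NE tonic and phasic activity profiles". The test set is then defined: "The model can then be applied to withheld data, that is, individuals who did develop transdiagnostic psychopathology". On the score itself the text adds: "This allows one to quantify a numeric deviation of LC-NE functioning from normative ranges". That deviation becomes the predictor of psychopathology in linear models.

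The same section plans v-fold validation and, later, external validation in independent data from the outpatient clinic. The missing-data paragraph under Ethical Considerations mentions v-fold again, as a check of predictive stability. Neither place says whether the norm is re-estimated inside the folds.

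On size, Work Package 4 states: "The full sample consists of the 300 participants assessed in task 2.2". Main Objectives sets clinical relevance at a CBCL T-score above 60. Under Expected Outcome, Work Package 4 looks for explained variance beyond previous psychopathology, childhood adversity and cognitive ability, and plans to use the spatial direction of the deviation.

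**The concern.** Training and withheld data are divided by the outcome that the score is meant to predict. A child used to estimate a mean and covariance lies, on average, closer to that mean than a new child from the same population. If non-cases are scored with the norm they helped to build while cases are scored as new children, cases look more deviant for a reason unrelated to the pupil. If instead only the withheld cases are scored, no non-case has a valid score, and the outcome range is cut at T 60.

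The risk tool is what the study intends to carry into the clinic. Its internal performance would therefore be either optimistic or incomplete. The stated target is future psychopathology, yet Work Package 4 does not say how children already above the cutoff at T1 are handled, and Recruitment says: "The main recruitment avenues will be the outpatient clinic for early detection at the Department for Child and Adolescent Psychiatry".

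**Working it through.** Work Package 4 states no AUC, explained variance or error rate, so there is no figure to reproduce. The check asks what the stated split produces when LC-NE functioning is unrelated to outcome.

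**Inputs from the article.** N = 300. Four tasks, with baseline pupil size (BPS) and stimulus-evoked pupillary response (SEPR) in each. Cutoff T > 60. Mean retention of 73.5% is cited under Task 3.1, and 300 × 0.735 ≈ 220.

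**Assumptions.** Case share 20–50%. Gaussian features. Number of features p from 2 (BPS and SEPR) to 8 (2 metrics × 4 tasks), with 16 and 24 if split further. CBCL SD 10.

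**1. All children scored, unsigned deviation.** Take the squared Mahalanobis distance from a norm fitted on n reference children.

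- In-sample mean: p(n−1)/n
- Out-of-sample mean: p(n+1)(n−1) / [n(n−p−2)]

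With n = 154 (70% of 220) and p = 8:

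- Non-cases: 8 × 153/154 = 7.95
- Cases: 8 × 155 × 153 / (154 × 144) = 8.56

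With p = 2 the pair is 1.99 and 2.05, almost no gap.

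The null simulation used 1000 runs per setting, N = 300 or 220, and case shares of 20, 30 and 50%. It compared cases with non-cases by a two-sided 5% t-test:

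| p | Null AUC | Rejection |
|---|---|---|
| 2 | .504–.508 | 4–7% |
| 8 | .522–.546 | 12–28% |
| 16 | .559–.627 | 37–94% |
| 24 | .604–.731 | 77–100% |

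With 4 features, separate runs gave about 6–10%. Adjusting the norm for covariates adds to the bias: at 8 features, rejection was 34–48% with three nuisance covariates and about 47–63% with five.

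**2. Signed single-metric score.** This is a linear rescaling of the raw metric. Null rejection was 4–6%, so there is no inflation.

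**3. Only cases scored.** Null rejection was 5%, so there is no false signal. The cost is range restriction: r′ = ru / √(1 − r² + r²u²), where u is the SD of the truncated outcome relative to the full SD. A cutoff 1 SD above the sample mean gives u = .446; a cutoff at the mean gives u = .603. For r = .30:

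- .1338 / √(.91 + .0179) = .139
- .1809 / √(.91 + .0327) = .186

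Simulation with r = .20 gave a case-only r of .09–.12 and rejection of 9–32%, against 85–95% when all children are used.

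**4. CBCL as the modelled output.** The section speaks both of a normative model of psychopathology and of a deviation of LC-NE functioning. If the residual were taken on CBCL, it would track case status with AUC .999 and no LC-NE signal at all, which is circular.

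**5. The remedy.** The norm was still fitted on non-cases only, but refitted in each of 10 folds, and held-out non-cases and cases were scored with the same out-of-fold norm. Null AUC was .496–.502 in all 24 settings. Rejection was 3.9–6.1%, with one setting at 7.7%.

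**The case against.** The strongest reply is that the article describes the norm in terms of tonic and phasic activity. That may mean just two metrics, for which the bias is negligible. Expected Outcome stresses simplicity and uses direction, so signed scores are plausible. Work Package 1 may shorten the battery. V-fold validation is already planned, its fold-level detail could sit in a fuller plan, and external validation would expose optimism. All of this limits the size of the problem. It does not remove the problem, because the article itself defines the withheld data as cases. External validation would come after the internal performance claim.

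Several stronger readings are tempting but not supported:

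- A reader might infer that scores must differ by construction, so the tool always looks predictive. Steps 1 to 3 show that this depends on the score and the feature count.
- A reader might infer that v-fold cannot help because the norm is defined by outcome. Step 5 shows that it can, if the norm is refitted and non-cases are held out.
- A reader might combine upward bias with truncation at T 60. These belong to different readings: the first needs all children scored, the second only cases.
- A reader might infer that children above T 60 at T1 are counted as having developed psychopathology, and that they are common. The article says neither. It also recruits from the general population, and its planned comparison with previous psychopathology partly addresses baseline status.
- A reader might take the covariate-adjusted rates as what the plan implies. Work Package 4 names covariates only as comparators, not as part of the norm.
- A reader might infer that features are selected on outcome in the same children. The text says only that findings of Objectives 2 and 3 enrich the model. The battery reduction it describes is in Work Package 1, for which Table 1 lists no CBCL.

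**Conclusion.** The point holds in a conditional form. As written, no non-case is held out and refitting within folds is not stated. If all children are scored with an unsigned multivariate deviation, the error favours the tool: negligible at 2 features, 12–28% false positives with AUC .52–.55 at 8, and more with further features or with covariates in the norm. Signed single-metric scores are unaffected. If only cases are scored, the result is not a false signal but an inestimable specificity and an attenuated association (.30 to about .14–.19). Even the 8-feature AUC is close to chance, so the practical harm there is a significant association reported where none exists, not a seemingly accurate tool.

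The sizes rest on the assumed case share, feature count and Gaussian features, none of which the article fixes. The handling of children already above the cutoff at T1 is unstated; that is a gap to close, not a demonstrated error. The figure of 300 is the number assessed in Task 2.2. The number with a known later outcome would be about 220 if the cited mean retention applied.

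**What to change.** Reword Work Package 4 as follows:

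- Define withheld data to include non-cases as well as cases.
- In each fold, fit the norm, and make any feature choice informed by outcome, on training-fold reference children only.
- Score held-out cases and non-cases with that same norm.
- Report association, AUC and calibration from held-out scores only.
- State that the deviation is of LC-NE measures, not of CBCL, and whether it is signed.
- Report children at or below T 60 at T1 who later exceed it separately from those already above it at T1.
- Give the number with a known follow-up outcome in place of 300.

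The cost is some wording and computing. Apparent accuracy will probably be lower, and the incident group will be smaller than the pooled case group. No new data are needed.
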